### **Blood sampling**

More detailed immunological studies (details below) will be conducted on a nested cohort, which will require larger volume blood draws at certain time points (details below). In order to identify this nested cohort, participants will be further divided into 2 sampling groups: Group A (30 participants) and B (90 participants). Allocation to sampling groups (i.e. A vs. B) shall be done randomly and stratified by vaccination group (i.e. 1 ChAd63/MVA ME-TRAP vaccinee for each control vaccinee). See tables 2 and 3 below.

20 mls of blood will be collected at screening (similar for both sampling groups) to test eligibility, which will be used for;

- Full blood count
- Serum ALT and creatinine
- HIV antibody testing (pre vaccination only) and Hepatitis B surface antigen
- Baseline *P. falciparum* PCR assay

40 mls of blood will be collected on days 0, 14, 63 and 161 for group A and at day 63 for group B. The following tests will be performed at these time points;

- Full blood count
- Serum ALT and creatinine

- Cellular immunology studies
- Plasma for antibody studies of immunity to malaria antigens.

10 mls of blood will be collected at day 56 for group A and at days 0, 14, 56, and 161 for group B. The following tests will be performed at these time points;

- Full blood count
- Serum ALT and creatinine

10mls of blood will be collected at Days 1 and 57 for Group A and stored for possible future gene expression studies.

Blood samples will be collected at day 63 and then between day 70 and day 119 for PCR monitoring. From day 70, blood samples will be collected three times per week for 4 weeks and then once per week for a further 4 weeks. Each blood sample will be taken by fingerprick (volume, 0.5-1.0ml), or, if the volunteer prefers, by venepuncture (volume, 2ml). See table 4 below for details of timing.

Where possible, blood samples will be stored for later immunological studies. This will allow further characterisation of the set of lymphocytes responding to the vaccine, and for exploratory immunology assessments to be done at the discretion of the investigators. Exploratory immunology assessments may include the following: HLA typing; DNA analysis of genetic polymorphisms potentially relevant to vaccine immunogenicity using sequencing or other genotypic methods; gene expression profiling; B cell ELISPOT; cytokine analysis; antivector immune responses; ELISA for measurement of antibodies to TRAP; and in vitro growth inhibition assays.

**Table 2: Group A sampling volumes (30 participants)**

| Clinic visit                        | 1  | 2  |          | 3   | 4   |          | 7    | 8-19                                                                                          | 20-23                                                            | 24      |
|-------------------------------------|----|----|----------|-----|-----|----------|------|-----------------------------------------------------------------------------------------------|------------------------------------------------------------------|---------|
| Field Worker Visit           |    |    | 1 |     |     | 2 |      |                                                                                               |                                                                  |         |
| Timeline (days)*             | S  | D0 | D1       | D14 | D56 | D57      | D 63 | Week 11: D70, 72, 74
Week 12: D77, 79, 81
Week 13: D84, 86, 88
Week 14 : D91, 93, 95 | Week 15: D98
Week 16: D 105
Week 17: D112
Week 18: D119 | D161    |
| Blood volume (mL)            | 20 | 40 | 10       | 40  | 10  | 10       | 40   | (0.5 – 2.0) x 12 = 6 – 24                                                                     | (0.5 – 2.0) x 4 = 2 – 8                                          | 40      |
| Cumulative blood volume (mL) | 20 | 60 | 70       | 110 | 150 | 160      | 200  | 206-224                                                                                       | 208-232                                                          | 248-272 |

**Table 3: Group B sampling volumes (90 participants)**

| Clinic visit                 | 1  | 2  | 3    | 4   | 7   | 8-19                                                                                          | 2-23                                                             | 24      |
|------------------------------|----|----|------|-----|-----|-----------------------------------------------------------------------------------------------|------------------------------------------------------------------|---------|
| Timeline (days)*             | S  | D0 | D 14 | D56 | D63 | Week 11: D70, 72, 74
Week 12: D77, 79, 81
Week 13: D84, 86, 88
Week 14 : D91, 93, 95 | Week 15: D98
Week 16: D 105
Week 17: D112
Week 18: D119 | D161    |
| Blood volume (mL)            | 20 | 10 | 10   | 10  | 40  | $(0.5 - 2.0) \times 12 = 6 - 24$                                                              | $(0.5 - 2.0) \times 4 = 2 - 8$                                   | 10      |
| Cumulative blood volume (mL) | 20 | 30 | 40   | 50  | 90  | 96-114                                                                                        | 98-122                                                           | 108-132 |

### **Laboratory procedures**

Because the laboratory immunology testing is expensive and labour intensive, cellular immunology will be conducted on all participants at the critical pre-surveillance time point only (i.e. day 63). We will randomly select 30 individuals (stratified by vaccination group) for cellular immunology studies on days 0, 14, and 161.

Plasma and cells will be stored at -20°C and -192°C respectively. ELISPOTs and fluorescence - activated cell sorter (FACS) studies following intracellular cytokine staining will be performed, and results validated by rigorous use of negative and positive controls. This technique uses an overnight stimulation by antigen of separated lymphocytes from the volunteer's blood sample to count the number of interferon gamma producing cells. Analysis by FACS, where sufficient numbers of lymphocytes are isolated, will allow further characterisation of the response, by co-staining lymphocytes with CD4 and CD8 as well as IFN gamma and other cytokines.

PCR studies will be undertaken firstly at King Baudouin hospital of Guediawaye. Blood will be filtered to remove white blood cells, and then DNA extracted from the full volume of blood. Real time PCR will be undertaken at UCAD, and a sub-set of the samples will be stored for further quality control studies in Oxford. This is because the method to be used at UCAD has been validated in Oxford.

### **Vaccine handling and administration**

Final batch certification and associated labelling of the IMPs, ChAd63 ME-TRAP and MVA ME-TRAP, is performed by the Qualified Person at the Clinical Biomanufacturing Facility (CBF), Churchill Hospital, Oxford, in accordance with Annex 13 and the CBFs internal SOPs.

Accountability, storage, shipment and handling of IMPs will be in accordance with relevant SOPs and forms. All movements of IMPs will be documented in vaccine accountability logs according to local site SOPs.

The IMPs are stored between  $-70^{\circ}\text{C}$  and  $-90^{\circ}\text{C}$  in a locked freezer at the University of Oxford, Churchill Hospital. The vaccines will be shipped from Oxford on dry ice then stored at  $-70^{\circ}\text{C}$  in a locked freezer at UCAD until required. Vaccines will be thawed on the morning of use, and kept in a cold box in the field. They will be used within 4 hours of thawing.

The rabies vaccine will be sourced locally. The rabies vaccines will be stored and used in accordance with the manufacturer's instructions.

All ChAd63 ME-TRAP, MVA ME-TRAP and rabies vaccinations will be given by intramuscular injection. A 23 gauge (G) needle and 1 ml syringe will be used.

Each volunteer will be monitored for 30 minutes (or longer if necessary) after each vaccination. Resuscitation (including intubation) equipment and medication will be available in the clinic site and a clinician trained in resuscitation present at all times.

### ***Indications for delayed vaccination.***

The following adverse events constitute contraindications to administration of vaccine at that point in time; if any one of these adverse events occurs at the time scheduled for vaccination, the subject may be vaccinated at a later date, or withdrawn at the discretion of the investigator. The subject must be followed until resolution or stabilization of the adverse event or until causality is determined to be unrelated to trial interventions, as with any adverse event.

- Acute disease at the time of vaccination. (Acute disease is defined as the presence of moderate or severe illness with or without fever). Vaccines can be administered to persons with a minor illness such as diarrhoea, mild upper respiratory infection with or without low-grade febrile illness, i.e., temperature of  $<37.5^{\circ}\text{C}/99.5^{\circ}\text{F}$ ).
- Temperature of  $\geq 37.5^{\circ}\text{C}$  ( $99.5^{\circ}\text{F}$ ) at the time of vaccination.

**NB:** Anaphylactic reaction following administration of study vaccine constitutes an absolute contraindication to further administration of vaccine, and the subject must be withdrawn and followed until resolution of the event

**Table 4: Summary of study visits**

| Clinic visit                       | 1         | 2  |    | 3   | 4   |     | 5       | 6   | 7   | 8-19                                                                                        | 20-23                                                           | 24    |
|------------------------------------|-----------|----|----|-----|-----|-----|---------|-----|-----|---------------------------------------------------------------------------------------------|-----------------------------------------------------------------|-------|
| Field Worker Visit                 |           |    | 1  |     |     | 2   |         |     |     |                                                                                             |                                                                 |       |
| Timeline (days)*                   | S         | D0 | D1 | D14 | D56 | D57 | D63     | D64 | D65 | Week11: D70,D72,D74
Week 12: D77,D79,D81
Week13: D84 ,D86,D88
Week14: D91, D93,D95 | Week 15: D98
Week 16: D105
Week 17: D112
Week 18: D119 | D161  |
| Window period (days)*              | -90 to -1 |    |    | ±7  | ±7  |     | -1 / +7 |     |     | -1/+4                                                                                       | -2/+4                                                           | -7/+7 |
| Vaccination                        |           | 1  |    |     | 2   |     |         |     |     |                                                                                             |                                                                 |       |
| Inclusion/ exclusion criteria      | ×         |    |    |     |     |     |         |     |     |                                                                                             |                                                                 |       |
| Informed consent                   | ×         |    |    |     |     |     |         |     |     |                                                                                             |                                                                 |       |
| Medical history                    | ×         |    |    |     |     |     |         |     |     |                                                                                             |                                                                 |       |
| Physical exam                      | ×         |    |    |     |     |     |         |     |     |                                                                                             |                                                                 |       |
| Safety Bloods^                     | ×         | ×  |    | ×   | ×   |     | ×       |     |     |                                                                                             |                                                                 | ×     |
| Contraindications review           | ×         | ×  |    |     | ×   |     |         |     |     |                                                                                             |                                                                 |       |
| Local & systemic events review     |           | ×  | x  | ×   | ×   | x   | ×       |     |     | ×                                                                                           | ×                                                               | ×     |
| Treatment with anti-malarial       |           |    |    |     |     |     | ×       | ×   | ×   |                                                                                             |                                                                 |       |
| P.falciparum PCR            |           | ×  |    |     |     |     | ×       |     |     | ×                                                                                           | ×                                                               |       |
| Immunogenicity Tests #             |           | ×  |    | ×   |     |     | ×       |     |     |                                                                                             |                                                                 | ×     |
| Blood sample for gene expression @ |           |    | x  |     |     | x   |         |     |     |                                                                                             |                                                                 |       |

^The following lab tests will be done: FBC, ALT, Creatinine.

Hepatitis B surface antigen test & HIV testing will also be done at screening.

\*Timeline is approximate only. Exact timings of visits relate to the previous visit – *i.e.* each visit must occur the specified number of days after the last visit  $\pm$  time window

\*All scheduled clinic visits will be done on week days

# Immunogenicity tests: 30 volunteers at D0, 14 and 161; all participants at D 63

@ Blood sample for gene expression: 30 volunteers at D1, and 57. This will be as close to 24 hours post vaccination as practicable.

## **Study Visits**

### **Screening visit: (Clinic visit)**

Medical history and physical examination will be performed at screening to exclude any significant medical conditions. The following lab tests will be done: FBC, ALT, rapid Hepatitis B surface antigen test, Creatinine and HIV testing.

### **D0 (Vaccination with ChAd63 ME–TRAP or Rabies vaccine) (Clinic visit)**

Medical history, temperature monitoring +/- physical examination will be performed and eligibility reviewed by the study clinicians prior to vaccination. Venepuncture for exploratory immunology (for 30 volunteers), safety assessment (FBC, ALT and Creatinine- all participants) and baseline PCR for *P. falciparum* for all participants will also be done prior to vaccination.

### **D 1 (Field worker visit)**

Each volunteer will be visited at home on day 1 by a field worker for assessment and recording of any solicited and unsolicited AEs in diary cards. If necessary, the volunteers will continue to be seen regularly until the symptom(s) have resolved or stabilised.

On day 1 the use of an insecticide treated net (ITN) by the volunteer will be assessed by observation in the homestead. Venepuncture for gene expression studies will be done on the 30 Group A volunteers, as close to 24 hours post-vaccination as practicable.

### **D14 (-/+7 days) (Clinic visit)**

Medical history, temperature monitoring +/- physical examination will be performed and recorded. Any solicited/ unsolicited AEs will be recorded. Venepuncture will be performed for FBC, ALT, Creatinine (all participants) and exploratory immunology (for 30 volunteers).

### **D56 (Vaccination with MVA ME–TRAP or Rabies vaccine) (-/+7 days) (Clinic Visit)**

Medical history, temperature monitoring +/- physical examination will be performed and recorded. Venepuncture will be performed for FBC, ALT and Creatinine (all participants). Eligibility will be reviewed by the study clinicians prior to vaccination.

#### **D 57 (Field worker visit)**

Each volunteer will be visited at home on day 57 by a field worker for assessment and recording of any solicited and unsolicited AEs in the diary card. If necessary the volunteer will continue to be seen regularly until the symptom(s) have resolved or stabilised. Venepuncture for gene expression studies will be done on the 30 Group A volunteers, as close to 24 hours post-vaccination as practicable.

#### **D63 (-1/+7 day) (Clinic Visit)**

Medical history, temperature monitoring +/- physical examination will be performed and recorded. Any solicited and unsolicited AEs will be recorded. Venepuncture will be performed for FBC, ALT, Creatinine, *P.falciparum* PCR analysis and exploratory immunology (for all participants).

1st day of Atovaquone/proguanil + Artesunate therapy

**D64 and 65 (Clinic Visit)** 2nd and 3rd day of Atovaquone/proguanil + Artesunate therapy

#### **Week 11, 12, 13 and 14**

Medical history, temperature monitoring +/- physical examination will be performed and recorded. Any solicited and unsolicited AEs will be recorded. Blood samples will be taken by finger-prick or venepuncture for *P.falciparum* PCR analysis.

#### **Week 15, 16, 17 and 18**

Medical history, temperature monitoring +/- physical examination will be performed and recorded. Any solicited and unsolicited AEs will be recorded. Blood samples will be taken by finger-prick or venepuncture for *P.falciparum* PCR analysis.

#### **Day 161 (±7 days) (Clinic Visit)**

Medical history, temperature monitoring +/- physical examination will be performed and recorded. Any solicited and unsolicited AEs will be recorded. Venepuncture will be

performed for FBC, ALT, Creatinine (all participants) and exploratory immunology (for 30 participants).

### **Concomitant therapy**

Any concomitant medication taken during the study period will be recorded.

## **Endpoints**

### **Primary Endpoint – Vaccine Efficacy**

We will compare active and control vaccination for time to first episode of *P.falciparum* infection, defined as 2 or more consecutive blood samples confirmed positive by PCR, for *P.falciparum*.

### **Secondary Endpoints**

Measures of immunogenicity will include:

Ex vivo ELISPOT responses to overlapping pools of ME – TRAP peptides.

Cultured ELISPOT responses to overlapping pools of ME – TRAP peptides.

ICS by flow cytometry for cell mediated immune responses

ELISA for antibodies to malaria antigens

All solicited and unsolicited local and systemic vaccine- linked adverse events (AEs) including clinically significant laboratory abnormalities.

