## **Methodology**

This is a single blinded randomised vaccine trial. The primary focus of the research will be directed at the impact of the proposed vaccine on the numbers of parasite carriers over a 2 month period following vaccination. This period will occur during the 2012 malaria transmission season.

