## **Study groups**

Subjects will be randomized to receive either ChAd63 ME-TRAP and MVA ME-TRAP or control vaccination with Rabies vaccine. To preserve blinding, Rabies vaccine will be administered in a 0, 2 month schedule. This differs from the standard schedule for rabies vaccination, however, administration of rabies vaccine by alternative schedules may still provide some protective efficacy against rabies. In addition, all participants will be offered a standard schedule of Rabies vaccine after the trial comes to an end.

Simple randomisation into the study groups will be done by an independent statistician and the study clinicians with an allocation ratio of 1:1 to study groups taking into account their area of residence. A randomization code list will be generated by an independent statistician and its use guided by a clear standard operating procedure (SOP). Allocation concealment will be employed by use of opaque sealed envelopes. The volunteers, fieldworkers and laboratory scientists will be blinded to vaccine allocation until the end of the study, but the clinical investigators will not be blinded.

All vaccinations will be administered by the intramuscular route – IM. Randomization into groups will be as follows:

- **Group 1**(60 volunteers): ChAd63 ME-TRAP  $5 \times 10^{10}$  viral particles (vp) followed by MVA ME-TRAP  $2 \times 10^8$  plaque forming units (pfu) 8 weeks later.
- **Group 2**(60 volunteers): control, i.e. Rabies vaccine 1ml followed by Rabies vaccine 1ml 8 weeks later.

Oral antimalarials will be taken by all participants from days 63-65 inclusive. The purpose is to clear any asymptomatic parasitaemia (both asexual blood stage parasites and gametocytes) prior to the commencement of PCR monitoring for new malaria infection from Day 70. A standard 3 day course of Atovaquone/proguanil will be combined with three days of concurrent oral artesunate. Atovaquone/proguanil has been chosen over artemether/lumefantrine to limit the potential for persistence of antimalarial drug from Day 70 when monitoring for new malaria infection commences (lumefantrine has a relatively long elimination half life). Artesunate has been selected because of its antigametocidal activity. The anti- malarial treatment will be directly observed.

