### **Definitions of adverse event categories**

#### **Adverse event**

Any untoward medical occurrence in a patient or clinical investigation subject occurring in any phase of the clinical study whether or not considered related to the vaccine. This includes an exacerbation of pre-existing conditions or events, intercurrent illnesses, or vaccine or drug interaction. Anticipated day-to-day fluctuations of pre-existing conditions, including the disease under study, that do not represent a clinically significant exacerbation will not be considered adverse events. Discrete episodes of chronic conditions occurring during a study period will be reported as adverse events in order to assess changes in frequency or severity.

Adverse events will be documented in terms of a medical diagnosis(es). When this is not possible, the adverse event will be documented in terms of signs and symptoms observed by the investigator or reported by the subject at each study visit.

Pre-existing conditions or signs and/or symptoms (including any which are not recognised at study entry but are recognised during the study period) present in a subject prior to the start of the study will be recorded on the Medical History form.

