**Table 5: Pain scale**

| Grade    | Description                                                                                                          |
|----------|----------------------------------------------------------------------------------------------------------------------|
| 0 | No pain at all                                                                                                       |
| 1 | Painful on touch, no restriction in movement of arms, able to work, drive, carry heavy objects as normal             |
| 2 | Painful when limb is moved
( i.e. restriction in range of movement in arm, difficulty in carrying objects) |
| 3 | Severe pain at rest
( i.e. unable to use arm due to pain.)                                                 |

All local reactions will be considered causally related to the vaccination in the absence of another more likely explanation (such as recent trauma).

At each visit subjects will be requested to report local and general side effects they might have experienced since they last were seen. The investigator will assess the severity of the solicited signs and symptoms using the key provided in Table 6.

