**Table 6: Intensity of the general adverse events will be assessed as described:**

|         |                                                                                           |
|---------|-------------------------------------------------------------------------------------------|
| GRADE 0 | None                                                                                      |
| GRADE 1 | Mild: Transient or mild discomfort (< 48 hours); no medical intervention/therapy required |
| GRADE 2 | Moderate: Mild to moderate limitation in activity - some assistance may be                |

|         |                                                                                                                                          |
|---------|------------------------------------------------------------------------------------------------------------------------------------------|
|         | needed; no or minimal medical intervention/therapy required                                                                              |
| GRADE 3 | Severe: Marked limitation in activity, some assistance usually required; medical intervention/therapy required, hospitalisation possible |

The investigator will use the guidelines provided below to assess the relationship of the event to the administration of the vaccine. Both severity of the event and its relationship to the vaccine administration will be documented in the CRF.

Further details for any AE (such as start/stop date and any treatment), will be gathered, regardless of the relationship to the vaccine. We will also document any unsolicited adverse event reported by the volunteer. Serious adverse events (SAE) as defined above will be documented and reported using a serious adverse event reporting form.

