### **Reporting of Adverse Events**

Every SAE occurring throughout the trial must be reported by telephone, e-mail or fax to the sponsor and DSMB by the investigator as soon as (s)he is alerted of it and within one working

day, even if the investigator considers the AE not related to vaccination. The investigator will then complete a SAE report as soon as possible and within 5 working days or 7 calendar days.

Any relevant information concerning the adverse event that becomes available after the SAE report form has been sent (outcome, precise description of medical history, results of the investigation, copy of hospitalisation report, etc.) will be forwarded to the sponsor in a timely manner, the anonymity of the subjects shall be respected when forwarding this information. Any study-related SUSAR or serious adverse event related to participation in the study must be reported to the ethical review committee (ERC) via email ([contact]) within twenty four (24) hours after the principal investigator (PI) becomes aware of the event. The hard copies of the report must be forwarded to the ERC Secretariat within three (3) working days of the initial notification. Follow-up reports should be submitted as soon as more information becomes available. Periodic safety reports of any study-related expected adverse event or adverse events not related to participation in the study will be forwarded to ERC.

Initial reports of SUSARs should be provided by the Sponsor to the Direction de la Pharmacie et des Laboratoires (DPL) as soon as possible but within seven calendar days of the notification of the SUSARs with follow up reports being provided within a further eight (8) calendar days.

The sponsor pledges to inform the authorities of any trial discontinuation and specify the reason for discontinuation.

The causal relationship between the SAE and the product will first be evaluated by the investigator with the following scale (table 7):

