***Safety data***

All reactogenicity analyses will be on an intention to treat basis, comparing control to malaria vaccine regimen. The frequency of adverse events, changes in ALT, plasma creatinine, haemoglobin, white cell count, platelet values will be described by time and vaccine group.

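### The secondary safety endpoint counts only adverse events judged vaccine-linked by unblinded investigators, while the safety analysis text has no such filter; the two define different outcomes

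*Protocol*

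**What the plan says.** **Endpoint.** Protocol section 9, Secondary Endpoints, gives one safety item: "All solicited and unsolicited local and systemic vaccine- linked adverse events (AEs) including clinically significant laboratory abnormalities".

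**Who judges linkage.** Section 10, in the text under Table 6, says "The investigator will use the guidelines provided below to assess the relationship of the event to the administration of the vaccine". For serious events, Reporting of Adverse Events says "The causal relationship between the SAE and the product will first be evaluated by the investigator with the following scale", which is the 0 to 4 scale of Table 7.

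**Who is blinded.** Section 9, Methodology: "This is a single blinded randomised vaccine trial". Study groups lists volunteers, fieldworkers and laboratory scientists as blinded, "but the clinical investigators will not be blinded".

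**What is analysed.** Section 13, Safety data, compares reactogenicity between control and malaria vaccine by intention to treat, and adds: "The frequency of adverse events, changes in ALT, plasma creatinine, haemoglobin, white cell count, platelet values will be described by time and vaccine group". It states no causality condition.

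**What is collected.** Section 10 defines an adverse event as one "occurring in any phase of the clinical study whether or not considered related to the vaccine", and the text under Table 6 has details gathered for any event irrespective of relationship. For local reactions, the text under Table 5 sets a default: "All local reactions will be considered causally related to the vaccination in the absence of another more likely explanation (such as recent trauma".

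**The concern.** In a randomised trial the comparison protected by randomisation is all events by arm. Keeping only events that someone judges to be caused by the vaccine adds a selection step after randomisation. If that person knows the allocation, the selection can differ by arm. It can produce a difference where there is none, or remove a real one if events among vaccinees are put down to malaria or another illness.

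Here the role that decides linkage is the one that is not blinded. The judgement also has room to move. Table 7 joins its criteria for *Possible* with *or*, so a plausible time relationship is enough alone. The protocol never says which Table 7 grade makes an event vaccine-linked.

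Safety and reactogenicity are a secondary objective (section 8), and the Rationale makes a later infant trial depend on the results of this trial and the parallel Kenyan one. The outcome counted should therefore be unambiguous.

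**Working it through.** The point rests on text. The protocol gives no adverse event rate, attribution rate or safety power to reproduce.

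**1. The two definitions side by side**

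| | Section 9, Secondary Endpoints | Section 13, Safety data |
|---|---|---|
| Events counted | Only those judged linked to vaccine | Adverse events, no condition |
| Laboratory | Clinically significant abnormalities, under the same heading of linked events | Changes in named values |
| Depends on a causality call | Yes | No |

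A report written to the first column need not match one written to the second. Nothing in the protocol says which prevails. The wording does not look like a slip of the pen: section 10, Follow-up of Adverse Events, also uses vaccine-linked in a causal sense.

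**2. Where the filter could act**

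- *Local reactions:* related by default in both arms, so there is little scope for differential attribution.
- *Serious events:* all are reported to the sponsor and the DSMB even if thought unrelated (section 10, Reporting of Adverse Events), so they stay visible.
- *Laboratory values:* produced by blinded staff and described by arm in section 13. Only the endpoint's clinically significant abnormalities pass through a linkage call.
- *Non-serious systemic and unsolicited events:* fully exposed, if section 9 governs.

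**3. Illustration of size (assumed rates)**

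Inputs: n = 60 per arm (section 9, Study groups). Assumed: the same true event rate r = 0.30 in both arms, and linkage probabilities a₁ (malaria vaccine) and a₀ (control).

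The proportion counted in each arm is r × a. The probability of a falsely significant result is the sum, over all pairs (i, j) with a two-sided Fisher p below 0.05, of Bin(i; 60, r·a₁) × Bin(j; 60, r·a₀).

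| Linkage a₁ v a₀ | Counted, r·a₁ v r·a₀ | P(Fisher p < 0.05) |
|---|---|---|
| No filter | 30% v 30% | 0.031 |
| 55% v 45% | 16.5% v 13.5% | 0.043 |
| 60% v 40% | 18% v 12% | 0.097 |
| 50% v 25% | 15% v 7.5% | 0.166 |
| 80% v 27% | 24% v 8% (rounded from 8.1%) | 0.591 |

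The apparent risk ratio equals a₁/a₀, because r cancels: 55/45 = 1.2, 60/40 = 1.5, 50/25 = 2.0 and 80/27 = 3.0. In every row the true ratio is 1.

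With other true rates, 60% v 40% linkage gives 0.06, 0.14 and 0.23 at r = 20%, 40% and 60%. Linkage of 70% v 30% gives 0.20, 0.51 and 0.78. Equal linkage of 50% v 50% stays at 0.02 to 0.03.

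**The case against.** The strongest reply is that section 13 is the only place that says how safety is compared, and it applies no filter. All events are defined and recorded whatever their cause, so the unfiltered analysis is already promised and its data already exist. A reader might infer from section 9 that the trial's between-arm safety comparison is filtered by knowledge of allocation. The documents do not support that: it would be true only if the endpoint wording overrode section 13, and nothing says it does. This part of the objection stands, and it limits the point to a conflict between two definitions, one of which is open to bias.

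It is also fair that the illustration rests wholly on assumed linkage rates, and that mild differences in linkage barely move the result (0.043 against 0.031). Section 13 says event frequencies will be described and names no test for them, so a rate of significant results measures something the protocol does not plan. The figures show how sensitive the filtered count is; they do not forecast what this trial would report.

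A third reply is that relatedness cut-offs and table layouts belong in the statistical analysis plan, which is not shown. That covers the cut-off. It does not cover the endpoint definition, which the protocol itself fixes: a plan faithful to section 9 would inherit the filter, and one faithful to section 13 would not report the stated endpoint.

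**Conclusion.** The point holds in a limited form. The safety endpoint as worded depends on a causality judgement by unblinded investigators, and it conflicts with the unfiltered description in section 13. If section 9 governs, the exposure is mainly to non-serious systemic and unsolicited events and to clinically significant laboratory abnormalities. Local reactions and serious events are largely protected.

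The size of any bias cannot be read from the protocol. With an assumed 30% event rate and 60 per arm, the chance of a falsely significant difference runs from about 4% to 59% across linkage splits from 55% v 45% to 80% v 27%, against 3% with no filter. It would be wrong to infer either that bias of this order is expected or that the planned safety comparison is already compromised. The change is still worth making: the endpoint is a stated one, the selection is avoidable, and the remedy is a small edit.

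**What to change.** 1. In section 9, Secondary Endpoints, remove the linkage condition, so that the endpoint is: *all solicited and unsolicited local and systemic adverse events, regardless of judged causality, by vaccine group*. Keep clinically significant laboratory abnormalities under the same rule.
2. In section 13, Safety data, refer to that definition, so that endpoint and analysis count the same events.
3. Report events judged related only as a supporting summary, and state which Table 7 grades count as related.

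The cost is a few words in two sections. No new data are needed, because all events are already recorded whatever their relationship, and no clinical procedure changes. The edit removes the causality filter only. The investigators who grade the severity of solicited signs and symptoms (text under Table 5) would still know the allocation, and the report should say so.
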